## Abstract

More than half of university students have high levels of stress. Stress management programs can help students improve coping skills and prevent psychological distress. However, studies have generally targeted all university students regardless of whether they experience high levels of stress or not, and thus more studies are needed to examine the feasibility and acceptability of e-health interventions for students with elevated stress. The present open trial aims to examine the feasibility and acceptability of a guided internet-based stress management program for university students with high levels of stress. In this study, participants are recruited via e-mail, newsletters, and flyers from four universities in the Netherlands to participate in a guided internet-based stress management program. Guidance is delivered by e-coaches who provide weekly asynchronous text-based motivational feedback after each module is completed. Primary outcomes are satisfaction with the intervention, assessed by the Client Satisfaction Scale (CSQ-8), and usability, assessed by the System Usability Scale (SUS-10). Secondary outcomes are perceived stress, quality of life, and depression, assessed by the Perceived Stress Scale (PSS-10), the EuroQol- 5 Dimension- 5 Level Scale (EQ- 5D- 5L), and the Patient Health Questionnaire (PHQ-9) respectively. Adherence rates to the program are assessed by examining the number of completed modules, time spent on the platform, and completed exercises. The Caring Universities Project was funded in (September 2019). In June 2020, the project was officially announced to the students and recruitment began immediately. As of October 2020, recruitment continues. The expected date of the publication of the results is in 2021. It is expected that the results of the proposed study will be informative for designing and implementing e-health interventions in higher education. Moreover, it is assumed that the findings will contribute to the growing literature on internet interventions by yielding preliminary evidence related to the feasibility and acceptability of an online stress management program.

**Trial registration:**

Netherlands Trial Register NL8686; https://www.trialregister.nl/trial/8686

## Introduction

1

College years coincide with the developmental phase of emerging adulthood. In this period, individuals experience several life transitions such as gaining autonomy, changing social roles, and new responsibilities (Sussman and Arnett, 2014; Rickwood et al., 2005). The first onset of several psychological problems often occurs in this period of life (Kessler et al., 2007). Besides the positive experiences, a considerable number of university students experience several stressors related to academic demands, interpersonal problems, changing life-styles, and financial difficulties (Pierceall and Keim, 2007; Robotham, 2008). Studies have shown that 63–73% of college students report high stress levels (Leppink et al., 2016; Stallman, 2010; Saleh et al., 2017).

Although stressors can be a facilitator of motivation and increased performance (Strack et al., 2017), chronic stress is associated with the onset of mental health problems including sleeping difficulties (Amaral et al., 2018), depression (Vrshek-Schallhorn et al., 2015; Newcomb-Anjo et al., 2017), anxiety (Bergdahl and Bergdahl, 2002; Young and Dietrich, 2015), eating disorders (Torres and Nowson, 2007), substance use (Lijffijt et al., 2014), and suicide (Liu et al., 2019). Having high levels of stress can also be related to role impairment (Alonso et al., 2018), lower academic achievement (Shields, 2001), and dropout from university (Eisenberg et al., 2009; Pritchard and Wilson, 2003).

Stressors related to university life (e.g. academic demands, lifestyle changes, living away from home, etc.) are inevitable and common to almost all students. However, some students might need some form of support to be able to effectively cope with the stressors. Evidence-based interventions can help college students to acquire effective coping strategies and change their maladaptive reactions toward stressors (Regehr et al., 2013). Recent studies in young adults showed that stress management programs can reduce psychological distress (Kim et al., 2016), sleep problems (Dvořáková et al., 2017), depression (Breedvelt et al., 2018), and anxiety (Brennan et al., 2016).

Although college students experience high levels of stress, the utilization of campus mental health services is remarkably low due to several barriers (Ebert et al., 2019; Rosenthal and Wilson, 2008). Lack of perceived need for receiving help, preference for self-help, perceived stigma, negative attitudes toward the treatment, lack of time, and not being aware of the services at the campus are among the most important treatment barriers (Czyz et al., 2013; Eisenberg et al., 2007). In addition, cultural differences and language barriers were among the main reasons reported for the low uptake of on-campus counseling services by international students (Eisenberg et al., 2007; Hyun et al., 2007; Mori, 2000). Apart from the attitudinal barriers, system-related circumstances can also limit access to mental health support; these include long waiting lists and insufficient resources to meet the increased demands on counseling centers at universities (Watkins et al., 2012).

E-health interventions can be helpful in overcoming some of the aforementioned treatment barriers. The internet is used by college students for various purposes, including maintaining contact with friends or family members, building a social network, getting acquainted with the new university environment, educational reasons (Gray et al., 2010; Sleeman et al., 2016), and also for seeking health information (Horgan and Sweeney, 2010). Internet-based interventions could, therefore, be easily adopted by this population. Besides, internet interventions have additional benefits such as anonymity, flexibility in time, and easy, low-cost access to mental health support (Andersson and Titov, 2014; Ebert et al., 2017; Stallman and Kavanagh, 2018). Universities can also alleviate the growing demand for university counseling centers by offering internet interventions to their students.

Recently, studies on internet interventions have yielded promising results for a wide range of psychological complaints such as stress (Davies et al., 2014; Heber et al., 2017; Frazier et al., 2015; Heber et al., 2016), depression, and anxiety (Reyes-Portillo et al., 2014). However, only a limited number of interventions were designed according to the college students' needs. Given the specific sources of stress during the college years and the increased individual and societal benefits of maximizing the potential of college students, more attention should be given to the development and implementation of stress management programs in higher education. Moreover, existing stress management programs did not specifically target college students with high-stress levels. Although programs targeting general college student populations without screening for the problem (universal prevention) are essential to promote well-being in higher education (Conley et al., 2013), recent meta-analytic evidence showed that internet-based interventions targeting students at risk (indicated prevention) yielded larger effect sizes than those based on universal prevention (Conley et al., 2016; Harrer et al., 2019). Yet indicated prevention in this field has not been extensively investigated (Amanvermez et al., 2020). As a result, it is essential to examine the feasibility and acceptability of stress management interventions for college students with high levels of stress. Therefore, this study aims to evaluate the feasibility and acceptability of a newly developed internet-based stress management program for university students with elevated levels of stress. The secondary goal is to investigate the differences from pre-test to post-test for stress, depression, and quality of life. We also aim to examine the adherence rate of college students.

## Methods

2

### Study design

2.1

This study is an open trial of a guided internet-based stress management program. It employs a single-group pre- (t0) and post-test (t1) design. Five weeks after t0, t1 is administered. The present study is part of the World Health Organization (WHO) World Mental Health International College Student Initiative (WMH-ICS) (Cuijpers et al., 2019). The study protocol was approved by the Scientific and Ethical Review Board of all participating universities (Vrije University Amsterdam, Leiden University, Maastricht University, and Utrecht University). This study was also registered at the Netherlands Trial Register (Registration Number: NL8686).

### Study setting

2.2

The Caring Universities Project is being conducted in the four above-mentioned universities in the Netherlands.

### Participants

2.3

Participants are undergraduate or graduate students enrolled in the above-mentioned universities. Participants are screened in terms of their stress levels. According to the screening results, we include students with elevated stress levels based on the Perceived Stress Scale 10-item (PSS-10) (Cohen and Williamson, 1988a). We aim to recruit 50 students.

### Eligibility criteria

2.4

We include participants if they meet the following criteria: 1) aged 16 or older, 2) having enrolled as bachelor, master, or Ph.D. student, 3) having elevated levels of perceived stress (PSS-10 ≥ 20.4) at screening, 4) having given informed consent. Both domestic and international students are eligible to participate in the study.

There is no established cut-off score for the PSS-10. Following the procedures of previous studies in this field, we decided to use 20.4 as a cut-off score in our study calculating the one standard deviation (*SD* = 6.2) above the mean score of 14.2 which has been found in a general population sample between 18 and 29 years old (Cohen and Williamson, 1988b). Recent findings on the PSS-10 also showed similar descriptive findings for college students (Leppink et al., 2016; Klein et al., 2016).

Exclusion criteria are 1) self-reported severe symptoms of depression (as defined by a score higher than 20 on the Patient Health Questionnaire (PHQ-9) (Kroenke et al., 2001)) or 2) experiencing suicidal risk (as defined by a score of 2 or above on the PHQ-9 item nine or a score of 1 or above for the question “In approximately how many months during the past 12 did you think about how you might kill yourself or work out a plan of how to kill yourself?” or responding somewhat likely/very likely to the question of “How likely do you think it is that you will act on this plan in the next 12 months?”).

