#### Assessments

2.8.5

Overview of the assessments can be seen in Table 1.

**Table 1 t0005:** Measures and assessment points.

	Assessment points		
	T0	Tx	T1
Socio-demographics	X		
Client Satisfaction Questionnaire (CSQ-8)			X
System Usability Scale (SUS-10)			X
Perceived Stress Scale (PSS-10)	X		X
Quality of life (EQ-5D-5L)	X		X
Perceived Stress Scale (PSS-4)		X	
Patient Health Questionnaire (PHQ-9)	X		X

T0 = Pre-test.

Tx = Weekly assessments.

T1 = Post-test (5-week).

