### Statistical analysis

2.11

Descriptive statistics will be calculated to examine participants' satisfaction with the intervention, usability, and adherence. We conduct two-tailed paired *t*-tests using a significance level α = 0.05 to assess changes in the scores of PSS-10, PHQ-9, and EQ- 5D5L. In addition, qualitative analysis will be conducted to examine the participants' use of the intervention, their satisfaction with the intervention, adherence, e-coach evaluation, and feedback about the modules. Moreover, semi-structured interviews with the participants will be audio-recorded and the verbal data will be transcribed. After obtaining all of the transcriptions and written responses, a thematic analysis will be conducted to identify and categorize the themes about their experiences with the intervention (Clarke & Braun, 2017). First, we will code and organize the written data under meaningful themes. After categorization of the main themes, we will examine whether they include sub-themes. At the end of the analysis, we will interpret the results based on the themes (Braun and Clarke, 2006; Howitt, 2010).

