## Discussion

3

The present study aims to examine the feasibility and acceptability of an internet-based stress management program for college students with elevated levels of stress. In addition, this study will examine whether any improvements in stress levels, quality of life, and depression occur from pre-test to post-test. We anticipate that the stress management program will be perceived as feasible and acceptable by college students. Improvement in the stress, quality of life, and depression scores are also expected after receiving this program, but may not reach significance levels. Similar stress management interventions for college students showed promising results (Frazier et al., 2015; Harrer et al., 2018). However, internet-based stress management programs for pre-selected students with high levels of stress are scarce in the literature. Therefore, we believe that this study will be informative for the development and implementation of internet-based programs for at-risk students in tertiary education. In addition, stress and coping are closely associated with mental health problems such as depression and anxiety (Bergdahl and Bergdahl, 2002; Garnefski et al., 2002). Therefore designing stress management programs for college students can also be preventative for common mental health problems.

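### Students are selected on a high PSS-10 and the same scale is tested pre to post without a control group, so a significant fall cannot be read as improvement from the programme

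*Protocol article*

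**What the plan says.** All references are to the protocol article.

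- **Entry (2.4 Eligibility criteria).** Students qualify by "having elevated levels of perceived stress (PSS-10 ≥ 20.4) at screening". The cut-off was obtained by "calculating the one standard deviation (*SD* = 6.2) above the mean score of 14.2", a mean taken from a general-population sample aged 18 to 29. The section adds: "Recent findings on the PSS-10 also showed similar descriptive findings for college students".
- **Design (2.1 Study design).** "It employs a single-group pre- (t0) and post-test (t1) design". "Five weeks after t0, t1 is administered".
- **Test (2.11 Statistical analysis).** Two-tailed paired t-tests are planned, "using a significance level α = 0.05 to assess changes in the scores of PSS-10, PHQ-9, and EQ- 5D5L".
- **Timing (2.8.5 Assessments).** Table 1, "Measures and assessment points", lists the PSS-10 at T0 (pre-test) and T1 (post-test) only. It has no screening column.
- **Intended reading (3 Discussion).** "this study will examine whether any improvements in stress levels, quality of life, and depression occur from pre-test to post-test". The same paragraph expects improvement once students have received the programme, but warns that it may not be significant.
- **Limitations (3 Discussion).** These cover sample size, dropout, e-coach experience, generalizability, Dutch psychometrics, the EQ-5D-5L ceiling and unmeasured stressors. Neither regression to the mean nor the absence of a control group is named.

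**The concern.** A group chosen because a fluctuating score was high on one occasion will on average score lower on the next, with or without treatment. The paired t-test compares the mean change with zero. In a sample truncated at one SD above the mean, and with the selecting score as baseline, zero is not the change to expect from an inactive programme. There is no control arm to show what that change would be.

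What is at stake is interpretation. A fall in PSS-10 with p < 0.05 would naturally be reported as improvement following the programme, and the limitations as written give the reader no warning. The one caution offered, that changes may fail to reach significance, points to a false negative. Where the screening score is the baseline, the larger risk is an artefactual positive.

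**Working it through.** **Inputs from the article.** Mean 14.2, SD 6.2, cut-off 20.4 (2.4); target of 50 students (2.3, 2.9); two-sided paired t-test at 0.05 (2.11).

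**Assumptions.** The article gives no test-retest correlation r over five weeks, so r is varied from 0.6 to 0.9. Scores are taken as bivariate normal, with no programme effect and no time trend.

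**Step 1: the article's own figure.** 14.2 + 6.2 = 20.4, reproduced. No power calculation was done, so there is none to check.

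**Step 2: mean at entry.** The cut-off is 1 SD above the mean. The truncated-normal factor is λ = φ(1)/(1 − Φ(1)) = 1.525. The mean among those selected is 14.2 + 6.2 × 1.525 = 23.66, which is 9.46 points above the population mean.

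**Step 3: expected fall with zero effect, if the screening score is t0.** The expected fall is (1 − r) × 9.46. The SD of the change is the square root of (1 − r)² × Var(selected score) + 6.2² × (1 − r²), with Var(selected score) = 6.2² × (1 + 1.525 − 1.525²) ≈ 7.65. The probability of a significant fall with n pairs follows from the non-central t distribution. It was also simulated with scores rounded to whole points, limited to 0–40 and selected at the cut-off.

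| r | Expected fall | SD of change | P(significant fall), n = 50, formula | Simulated, n = 50 | Simulated, n = 25 |
|---|---|---|---|---|---|
| 0.6 | 3.8 | 5.1 | >99% | >99% | 95% |
| 0.7 | 2.8 | 4.5 | 99% | 99% | 87% |
| 0.8 | 1.9 | 3.8 | 94% | 95% | 68% |
| 0.9 | 0.9 | 2.7 | 68% | 69% | 41% |

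For comparison, a two-sided 5% test gives a significant fall in 2.5% of trials when the true mean change is zero. The n = 25 column shows what heavy dropout would do; the article gives no dropout rate.

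**Step 4: a more stressed source population (assumption).** If the student mean were already 20.4, then λ = 0.798 and the fall is (1 − r) × 6.2 × 0.798. That is 2.0, 1.5, 1.0 and 0.5 points for r = 0.6, 0.7, 0.8 and 0.9. The probability of a significant fall at n = 50 is 75%, 62%, 44% and 24%.

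**Step 5: a separate t0 after screening (assumption).** Mean 14.2, n = 50, correlation between t0 and t1 of 0.7, simulated:

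| corr(screening, t0) | corr(screening, t1) | P(significant fall) |
|---|---|---|
| 0.7 | 0.7 | 3% |
| 0.8 | 0.7 | 28% |
| 0.7 | 0.6 | 27% |
| 0.8 | 0.6 | 80% |
| 0.7 | 0.49 | 84% |

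If the screening score correlates equally with t0 and t1, all the regression has happened by t0 and none is left for the test. If the correlation fades with time, part of it remains.

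**The case against.** The strongest objection is that the high rates need the screening score to be t0, and the article does not say so. Section 2.4 speaks of screening, while 2.1 and Table 1 speak of t0. The main route in 2.10 Recruitment is a separate survey, after which eligible students are invited and asked for consent, so a fresh t0 is quite possible. Table 1 does not settle it: it also omits the suicide-risk screening questions, so it is not a full list of what is asked at screening. This stands, and it makes the size of the problem conditional.

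A reader might therefore infer that regression to the mean will usually produce significance here. The documents do not support that much. Besides the t0 question, r is not given. The Introduction cites 63–73% of college students reporting high stress, whereas a mean of 14.2 and SD of 6.2 put only about 16% above the cut-off. Section 2.4 calls student scores similar, so the text points both ways on the mean. Dropout is expected.

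A reader might also say that the test has the wrong significance level. Strictly, it tests zero mean change, and if regression to the mean shifts the mean, rejecting zero is correct. The error would lie in crediting the programme.

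Nor can the argument simply be extended to the PHQ-9. No calculation supports it, and excluding students with high PHQ-9 scores truncates that scale in the opposite direction.

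Finally, PSS-10 change is a secondary outcome of a feasibility study, and no decision depends on its p-value. This also stands and limits the severity. It does not remove the point: pre-post change is a declared goal, it carries an inferential test, and improvement is expected after the programme.

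**Conclusion.** The concern holds in a conditional form. With entry at one SD above the mean, the same scale as outcome and no control group, a significant fall in PSS-10 cannot be read as programme benefit.

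How misleading the test would be depends on facts the article leaves open. If the screening score is t0 and the article's mean and SD apply, 50 pairs give a significant fall with no programme effect in about 69% to more than 99% of trials (r assumed, 0.9 to 0.6), with an expected fall of about 1 to 4 points. At a student mean of 20.4 the range is about 25% to 75%. With a separate t0 it runs from the nominal level to over 80%. The satisfaction and usability outcomes are untouched. Severity is moderate: the reading of a secondary outcome needs correcting, but the study's main purpose is not compromised.

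**What to change.** 1. **2.8.5 Assessments:** state that t0 is a PSS-10 completed after screening and consent, and that the screening score is never the baseline. Students already enrolled without such a score should be reported separately or in a sensitivity analysis.
2. **2.11 Statistical analysis:** report PSS-10 change as a mean with 95% confidence interval, and state that p < 0.05 will not be read as programme benefit. Where the screening score has to serve as baseline, the fall expected from regression to the mean may be shown over a stated range of r, as a sensitivity display only. It should not become a threshold that the observed change must exceed: r is unknown, and once a fresh t0 is used the subtraction would correct twice.
3. **3 Discussion, limitations:** add regression to the mean and the absence of a control group.

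The cost is ten more questionnaire items per student, a few lines of analysis and text, and a less favourable headline for the change score. Recruitment began in June 2020 and was continuing in October 2020, so a change made during recruitment also leaves a mixed baseline definition, which item 1 has to handle.

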### E-coaches

2.6

Participants receive feedback from the e-coaches after completing each module. E-coaches are (research) master students in clinical psychology and 3rd-year clinical psychology bachelor students (at the end of the 2nd semester) who meet the criteria of specific courses namely 1) coaching and assessment, 2) low-intensity treatments for common mental health problems, and 3) diversity in clinical practice. The e-coaches were selected in the following way: After attending an informative meeting, interested students responded in writing, outlining their motivation to be an e-coach in this project. Selected students were invited for an interview with the research team. After completing the selection, students completed 5 1/2 hours of training including a supervised intervision meeting during which the e-coaches discuss their feedback in a plenary session. These e-coaches are regularly supervised by the research team, including a clinical psychologist, for the duration of the intervention. E-coaches will provide asynchronous written personalized feedback to each participant via the intervention platform. The written feedback aims to increase motivation and adherence. Participants also receive automatic reminders to increase engagement in cases of two weeks of inactivity.

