##### Depressive symptoms

2.8.2.2

The PHQ-9 is used to assess depression (Kroenke et al., 2001). Each item is rated on a 0–3 scale. Higher scores indicate a higher level of depressive symptoms. The scores of 1–4, 5–9, 10–14, 15–19, and 20–27 indicate no depression, mild depression, moderate depression, moderately severe depression, and severe depression, respectively (Kroenke et al., 2001).

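### The depression exclusion starts at PHQ-9 of 21, but the protocol's own severe band starts at 20, so a score of exactly 20 is severe yet not excluded on depression

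*Protocol article*

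**What the plan says.** Section 2.4 (Eligibility criteria) lists as its first exclusion "self-reported severe symptoms of depression (as defined by a score higher than 20 on the Patient Health Questionnaire (PHQ-9"). The second exclusion, suicidal risk, is met by "a score of 2 or above on the PHQ-9 item nine" or by a positive answer to either of two questions on suicidal thoughts and plans. It does not depend on the PHQ-9 total.

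Section 2.8.2.2 (Depressive symptoms) describes the same instrument: "Each item is rated on a 0–3 scale", and "The scores of 1–4, 5–9, 10–14, 15–19, and 20–27 indicate no depression, mild depression, moderate depression, moderately severe depression, and severe depression, respectively". Both sections cite the same source for the scale. Nothing in the article explains why the exclusion should begin one point above the severe band.

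On delivery, section 2.6 says: "E-coaches are (research) master students in clinical psychology and 3rd-year clinical psychology bachelor students".

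**The concern.** Section 2.4 does more than choose a cut-off. It says that the cut-off defines severe symptoms. The article then prints a second definition of severe that starts one point lower. Section 2.4 governs entry, so at a score of 20 the rule as written admits, on depression, a student whom the protocol elsewhere classes as severe.

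The criterion reads as a protective one. The programme targets stress, and its guidance comes from psychology students. Under section 2.10, students who do not meet the criteria are told about other sources of help. A student at 20 could be enrolled instead of being directed to that help, and readers would be told that severe depression was excluded when the rule does not quite do that.

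**Working it through.** **Inputs.** Excluded on depression: PHQ-9 above 20 (section 2.4). Severe band: 20–27 (section 2.8.2.2). Items scored 0–3 (section 2.8.2.2); nine items give integer totals from 0 to 9 × 3 = 27. Suicide-risk rule on item nine: 2 or above (section 2.4). Target sample: 50 (section 2.9).

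**Comparison of the two definitions.**

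| Definition | Totals | Number of scores |
|---|---|---|
| Excluded as written (above 20) | 21–27 | 7 |
| Severe band | 20–27 | 8 |
| Severe but not excluded on depression | 20 | 1 |
| Excluded if the rule is 20 or higher | 20–27 | 8, none discordant |

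**Does the item-nine rule catch a total of 20?** The other eight items can sum to at most 8 × 3 = 24. With item nine at 0 they must sum to 20; with item nine at 1 they must sum to 19. Both are within 24, so both are attainable and neither triggers the item-nine exclusion.

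The response patterns can be counted by points lost from the maximum, removing patterns in which one item loses more than 3:

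- item nine = 0, the others lose 4 points: C(11,7) − 8 × C(7,7) = 330 − 8 = 322
- item nine = 1, the others lose 5 points: C(12,7) − 8 × C(8,7) = 792 − 64 = 728
- all nine-item patterns that total 20 (7 points lost): C(15,8) − 9 × C(11,8) = 6435 − 1485 = 4950

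So 322 + 728 = 1050 of 4950 patterns pass the item-nine rule. This shows attainability only. Patterns are not equally likely, and the two further suicide questions are not counted.

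**How many students?** The article gives no PHQ-9 distribution, so the share p of enrolled students scoring exactly 20 is assumed. With n = 50, the expected number is 50p, and the chance of at least one is 1 − (1 − p)^50.

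| Assumed p | Expected number | Chance of at least one |
|---|---|---|
| 0% | 0 | 0% |
| 0.5% | 0.25 | 22% |
| 1% | 0.5 | 39% |
| 2% | 1 | 64% |

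**The case against.** The strongest reply is that this is a label one point out, not a fault in the design. The entry rule is explicit, and no screener would be unsure what to do with a score of 20. The bands in section 2.8.2.2 serve to interpret a secondary outcome and are loose themselves: the lowest starts at 1, leaving 0 unclassified. The rule already admits moderately severe depression (15–19), so the added exposure is one adjacent point on a self-report scale. Other safeguards exist: the suicide-risk exclusion is broad, e-coaches are trained and supervised by a team that includes a clinical psychologist (section 2.6), and section 2.12 sets out a suicide prevention protocol. The probabilities above only restate assumed shares. Finally, recruitment was continuing in October 2020 under a protocol approved at all participating universities, so moving an eligibility cut-off may be more than an edit.

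Much of this stands as a limit on size. The safeguards reduce the consequence, the number affected is unknown, and the cost may include notifying the review boards. None of it removes the mismatch. The rule can be applied without doubt, but what it does differs from what it is said to do. The unclassified score of 0 has no bearing on the severe boundary. The supervision and the suicide protocol act after enrolment, whereas the criterion is meant to act before it.

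**Conclusion.** The concern holds. The depression exclusion and the severe band disagree at exactly one attainable score, 20, and the suicide-risk criteria do not fully cover it. This follows from the printed text and from integer scoring, with no outside assumption. It should be corrected because it is an operative threshold in an exclusion that bears on safety.

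Its practical size is small. The primary outcomes (CSQ-8 and SUS-10) and the planned analysis are unaffected. The number of students concerned may be zero; only the illustrative range of 0 to 1 expected among 50 rests on an assumption. It may also be a wording slip, with screening already set at 20 or above, which the article alone cannot settle.

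**What to change.** Change the section 2.4 criterion to a PHQ-9 score of 20 or higher. That reproduces the 20–27 band with no discordant score. Confirm which boundary the screening actually applies, and report how many students have already been enrolled with a score of exactly 20.

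If a cut above 20 was intended, keep it, stop describing it as excluding severe depression, and state that a score of 20 is admitted.

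The cost is a one-line correction, a check of the screening rule and a look-up in data already held. If screening has been running at above 20, lowering the cut during enrolment may also need a minor notification to the review boards. The relabelling option leaves the cut-off itself unchanged.
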